**Table 1 Tab1:**
[figure not shown]
Simple Suppers Intervention Study Design: Two-Group, Staggered Cohort Quasi-Experimental Design

Following baseline data collection, families will decide whether to enroll in either the upcoming 10-week session of Simple Suppers (intervention group) or to wait for 10-weeks (waitlist control group) after which time they would begin the Simple Suppers program. Randomization of families is not feasible because of scheduling conflicts with participating families, the desire of families to participate in the program with families they know, and the need to establish trust with the site/participating families; thus, to preserve sample size and establish trust with the site/participating families, the personal preference of participating families will determine group membership.

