### Intervention

The Intervention Mapping protocol was utilized in the development of the Simple Suppers intervention [16, 17]. Formulation of proximal program objectives occurred as the first step in the mapping process. Based on the current evidence linking family meals with improved child diet and weight status [2–5], the following program objectives were formulated: 1) ‘Increase frequency of family meals prepared in the home (≥5 days/week)’ and 2) ‘Improve child diet quality (significantly increase Healthy Eating Index (HEI) score (*p* < 0.05); increase servings of fruits and vegetables to meet Dietary Guidelines recommendations; significantly decrease daily servings of sugar sweetened beverages (*p* < 0.05)’ (Table 2).

**Table 2 Tab2:** Overview of formulated program objectives at each level of intervention

Program objective	Level of Intervention	Target group	Performance Objectives
1. Increase frequency of family meals prepared in the home (≥5 days/week)^a^	Individual	Child	PO1. Children participate in cooking activities
	Interpersonal	Caregiver	PO2. Caregivers identify health benefits of regular family meals prepared in the home PO3. Caregivers plan well-balanced weekly dinner menus that include ≥1 svg from 3 of the 5 food groups PO4. Caregivers plan when and where family meals will be served in the home PO5. Caregivers use list for grocery shopping PO6. Caregivers use cost-saving strategies for family meals in the home PO7. Caregivers use time-saving strategies for family meals in the home
2. Improve child diet quality (significantly increase HEI score (*p* < 0.05); increase daily svgs of fruits, vegetables to Dietary Guidelines recommendations;^b^ significantly decrease daily svgs of: SSBs (*p* < 0.05 decrease)^c^	Individual	Child	PO1. Children know health benefits of eating well-balanced meals and snacks PO2. Children participate in planning/preparing well-balanced family meals ≥2x/week
	Interpersonal	Caregiver	PO3. Caregivers know benefits of serving well-balanced meals/snacks PO4. Caregivers serve family meal in the home that include ≥1 svg from 3 of the 5 food groups ≥1x/week PO5. Caregivers serve ≥3 snacks/week that include ≥1 serving from 2 food groups PO6. Caregivers buy food for planned meals/snacks at grocery store

*PO*: Performance objective *HEI*: Healthy Eating Index *SSB*: Sugar sweetened beverage *Svg*: Serving

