^a^Measured by asking the question, “During the past 7 days, how many times did all or most, of your family eat dinner together?”[7]

^b^U.S. Departments of Agriculture and Health and Human Services. Dietary Guidelines for Americans, 2010. 7th ed., Washington, DC. December, 2010 [18]

^c^Measured by 24-h dietary recall [29]

Matrices containing the behavioral performance objectives relating to each program objective were created for each level of intervention: individual (child) and interpersonal (caregiver) (Table 2). Development of the performance objectives were guided by the evidence-based 2010 Dietary Guidelines for Americans guidelines for families and children [18]. For example, under program objective 1) (family meals), the performance objective at the individual (child) level was ‘Children participate in cooking activities’ and at the interpersonal (caregiver) level, ‘Caregivers identify health benefits of regular family meals prepared in the home’.

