4	Connecting with your child through family meals	Involve child in 1 mealtime activity at 2 family meal occasions
5	Planning well-balanced family meals	Serve a family meal with 1 serving of whole grains, vegetables, and protein at 1 family meal occasion
6	Rethink your drink	Serve 1 well-balanced family meal with low-fat/no sugar added beverages
7	Making healthy cooking tasty & easy	Use 1 healthy cooking method to plan and serve 1 well-balanced family meal at 1 family meal occasion
8	Serving & eating healthy portions	Serve 1 well-balanced family meal with healthy portion sizes at 1 family meal occasion
9	Eating healthy when eating away-from-home	Eat 1 well-balanced, nutritious meal away-from-home at 1 family meal occasion
10	Planning fun & healthy snacks	Serve 2 planned, pre-portioned, well-balanced snacks to your child

Finally, the Simple Suppers program design was developed with feedback from program adopters (faith-based community center staff), implementers, and the target population [27] (e.g., utilizing two (versus one) educators for the caregiver component and incorporating site-based staff into the staffing structure). Each 90-min lesson is delivered weekly over the dinner hour. Session components include: a) interactive group discussion and goal setting with caregivers; b) hands-on activities with children; and c) group family meal with caregivers and children.

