### Sample size and data analysis

Sample size was determined by examining the power of the test for comparing increases in frequency of family meals (day per week) of the intervention and waitlist control group. The data used to estimate power come from a previous pilot study, in which the main outcome of interest was the change in frequency of family dinners prepared and eaten at home together (weekly basis) from baseline to post-intervention [42]. Change in frequency of family dinners was used to power the current study because there is strong evidence that it has a downstream effect on the outcome of interest, child BMI [3, 42–44], and there are no previous studies that show a causal effect of family dinners on BMI. Based on these data, assuming 20% attrition [42], with an expected effect size of 0.7071, there will be 80% power to detect a difference in frequency of family dinners of 3 days per week with 30 families per group for a total sample size of 60 families at α = 0.05. Because the sample size in the previous pilot study was small and uncertainty about estimated effect size was large, we used a conservative estimate of effect size (i.e., the lower bound of a 95% confidence interval) for the power calculation.

Data from each of the three cohorts will be pooled and the intervention tested by comparing change (T1-T0) in diet quality, anthropometric measures, and blood pressure of child and caregiver participants in the intervention compared to participants in the waitlist control (hypotheses 1.1 and 2.1). Multiple regression models will be used to determine the association between the difference in the response variables of interest between the intervention and control group, controlling for potential confounders (race/ethnicity, income, cohort, intervention dose), from baseline (T0) to 10-week post-test(T1) and 10-week follow-up (T2). For families in which data will be collected on multiple children, the effect of family will also be controlled by including a random effect for family.

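### The quoted family-dinner question counts any shared dinner, not only dinners at home, so the programme's own group meal can add up to one dinner in the intervention group at T1

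*Protocol article*

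**What the plan says.** **The question.** Footnote a to Tables 2, 3 and 5 (Intervention section) gives the measure for programme objective 1 as "During the past 7 days, how many times did all or most, of your family eat dinner together". The objective it is attached to is "Increase frequency of family meals prepared in the home (≥5 days/week", followed by the closing bracket.

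**The power basis.** Sample size and data analysis says that the pilot outcome used for power was "change in frequency of family dinners prepared and eaten at home together (weekly basis) from baseline to post-intervention".

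**The programme.** The Intervention section states "Each 90-min lesson is delivered weekly over the dinner hour", and one of the session components is a "group family meal with caregivers and children". Control families choose "to wait for 10-weeks (waitlist control group) after which time they would begin the Simple Suppers program" (text after Table 1).

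**Timing.** Study design places baseline in the two weeks before the programme starts and calls T1 the 10-week post-test. The Abstract puts that assessment at completion of the intervention. No minimum gap between lesson 10 and T1 is stated.

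**The outcome section.** Under Home environment, Family meals, the frequency of shared family dinners is one of four caregiver-reported items on a 5-point scale. The sources cited differ from the footnote's, and the item wording is not given.

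**The concern.** The question is broader than what it is said to measure. A caregiver who answers it literally should count the group dinner at the centre, because the family did eat dinner together. That dinner can enter the 7-day look-back only for intervention families at T1. Baseline precedes the programme, and controls start it after their wait. Any error would therefore favour the intervention, and neither blinded assessors nor adjustment for confounders would remove it.

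Two results could be affected. The T0 to T1 comparison for hypothesis 2.1 could show a gain that comes from attending the programme and not from dinners at home. By T2, ten weeks later, the group dinner is no longer in the look-back, so the T1 to T2 change could look like a loss of effect under hypothesis 2.2. Family-meal frequency is one of the main outcomes in the Abstract and the one on which the trial is sized.

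**Working it through.** **Inputs from the article (Sample size and data analysis):** target difference 3 days per week; effect size 0.7071; 30 families per group; 20% attrition, so 30 × 0.8 = 24 analysed; α = 0.05, sidedness not stated.

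**The plan's own figure.** Two-sample comparison of means, normal approximation, effect size 0.7071:
- one-sided, 24 per group: 78.9%
- two-sided, 30 per group: 78.2%
- two-sided, 24 per group: 68.8%

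The stated 80% is approached if the test is one-sided or if attrition is ignored. That is a separate matter and does not decide this point.

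**Implied SD.** 3 / 0.7071 = 4.24 days. The article describes 0.7071 as a lower confidence bound, so pairing it with 3 days is uncertain. It is still the only SD the document supports.

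**Size of the shift.** The group dinner counts only if T1 falls within 7 days of lesson 10 and the family attended. If it replaces a shared dinner the family would have had at home that evening, the net gain is zero. The mean shift therefore lies between 0 and 1 dinner. A full dinner is 1 / 4.24 = 0.24 SD, and 1 / 3 = 33% of the planned difference. A half dinner is an illustrative assumption: half of the families have lesson 10 inside the look-back, or half of the group dinners replace a home dinner.

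**Chance of p < 0.05 with no change at home.** Unadjusted two-sided t-test, 24 per group, 46 degrees of freedom. Noncentrality = shift / (SD × √(2/24)). At SD 4.24 the standard error is 4.24 × 0.2887 = 1.22, so a full dinner gives 1 / 1.22 = 0.82 and a half dinner 0.41. The SDs of 3 and 2 are assumptions; no document gives them.

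| SD of change (days) | Half-dinner shift | Full-dinner shift |
|---|---|---|
| 4.24 (implied by the plan) | 6.9% | 12.6% |
| 3 (assumed) | 8.7% | 20.4% |
| 2 (assumed) | 13.6% | 39.6% |

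The nominal level is 5%. With all 30 per group analysed, the implied-SD row becomes 7.3% and 14.6%.

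**The case against.** The strongest reply is that the footnote question may not be the trial's outcome item. It stands in the intervention-mapping tables as an open count. The outcome section describes scaled items from other sources under a home-environment heading, and the power section speaks of dinners at home. A reader might infer that the quoted question is the powered outcome; the documents do not establish that, and the link is an inference. It remains the only wording given. Apart from its heading, the outcome section's description has no at-home limit either, so the inference is reasonable but not certain.

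Second, an article commonly leaves counting instructions and exact visit windows to a fuller document. That stands: their absence is not a fault here. What the article does state is the mismatch between a question without a place limit and a construct defined as at home.

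Third, the full-dinner figures stack several conditions: every T1 visit within 7 days of lesson 10, every family attending, and no home dinner displaced. Process measures itself foresees irregular attendance. This also stands, and is why the half-dinner column is shown. A reader might take 20% to 40% as the expected false-positive rate, but those values need a full dinner as well as an assumed SD below the one the plan implies.

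Fourth, a reader might infer that the waitlist replication analysis (T2-T1) receives the same artificial gain. The text does not support this: the outcomes listed for that analysis are diet, body measurements and blood pressure, and family-meal frequency is not among them. The maintenance analysis differs, because its description cites hypothesis 2.2.

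**Conclusion.** The point holds in a limited form. The quoted question does not match the at-home construct of programme objective 1 or of the power calculation. If it, or a similarly unrestricted item, is asked within 7 days of lesson 10, it can credit the intervention group with between 0 and 1 dinner per week from programme delivery alone. At the plan's implied SD, the false-positive rate would be about 6.9% for half a dinner and 12.6% for a full one, against 5%; at an assumed SD of 2 to 3 days, about 9% to 14% and 20% to 40%. The same dinner can imitate a loss between T1 and T2.

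These figures assume no true change at home, 24 families per group and an unadjusted two-sided test on a count of dinners; the planned regression on a scaled item could differ. A reader might see a flaw that must be corrected before the trial can be interpreted. That goes too far: the item link is inferred, the shift may be close to zero, and the argument concerns only one of the three main outcomes. It is a worthwhile and inexpensive improvement.

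**What to change.** Use one and the same item in Table 2 (with the matching footnotes to Tables 3 and 5) and in the Family meals outcome section. At every visit, word it as dinners prepared and eaten together at home in the past 7 days, not counting Simple Suppers sessions. Alternatively, keep the question and time the T1 questionnaire so that the 7-day look-back starts after the last lesson.

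The cost is a few words in a caregiver questionnaire or a short assessment window. The drawback is slightly less comparability with studies that asked the question without these limits. It should be settled before T1 data are collected, because programme dinners cannot be reliably separated from home dinners afterwards.

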### Outcome measures

#### Children and caregivers

##### Diet quality

Dietary intake will be assessed by conducting three, nonconsecutive (two weekdays, one weekend day) 24-h (24 h) dietary recalls using USDA’s 5-step multi-pass dietary recall method [28]. At each data collection time point, the first dietary recall will be conducted during the in-person data collection visit, the remaining two will be conducted via telephone within two weeks of the initial in-person recall. For the child dietary recalls, caregivers will provide assistance, as caregiver-assisted 24 h recalls, collected in this way (i.e., relying on three days and utilizing the multi-pass method), provide the most accurate estimate of dietary intake among children 4 to 11 years of age [29]. Caregiver 24 h dietary recalls will be conducted independently following the child recall(s). Typical daily dietary intake will be determined by averaging dietary intake across the three recalls at each time point to determine daily servings of fruit, vegetables, and SSB. Diet quality will be assessed at each point by calculating a Healthy Eating Index 2010 score using the three 24 h dietary recalls collected [30].

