### Study design

The study will be implemented over 12-months as a two-group (intervention; waitlist control) quasi-experimental trial using a staggered cohort design (Table 1). At each of three time periods, separated by 10 weeks, a cohort of 20 families will be recruited. Each cohort will be divided into an intervention and waitlist control group (10 families in each). Consequently, a total of 60 families (30 in the intervention group and 30 in the waitlist control group) will be enrolled. Upon confirmation of study eligibility, a baseline data collection appointment will be scheduled at the participating family’s home or the community center during the two weeks preceding intervention commencement. Data will be collected on the primary food preparing caregiver and all children 4–10 years old. Written caregiver consent and child assent will be obtained. Data will be collected on all outcomes via direct measure and questionnaires at baseline (time point 0, T0), 10-week post-test (time point 1, T1), and 10-week follow-up (time point 2, T2). Repeatability of the intervention (replication) will be evaluated by assessing measures on the waitlist control group at T1 and T2. Assessments will last up to 90 min. A team of trained research staff, blinded from group assignment, will facilitate data collection. Caregiver participants will receive a $25 grocery store gift card at each data collection point for their participation in the research. All study materials and procedures have been approved by the Institutional Review Board at Ohio State University.

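### The stated visit and telephone windows let baseline diet recalls in the intervention group fall after lesson 1

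*Protocol article*

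**What the plan says.** Under Study design, the baseline appointment takes place "during the two weeks preceding intervention commencement". Under Diet quality, each time point uses "three, nonconsecutive (two weekdays, one weekend day) 24-h (24 h) dietary recalls". On timing, "At each data collection time point, the first dietary recall will be conducted during the in-person data collection visit", and "the remaining two will be conducted via telephone within two weeks of the initial in-person recall". The three recalls are combined by "calculating a Healthy Eating Index 2010 score using the three 24 h dietary recalls collected".

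The text below Table 1 gives the order of events: "Following baseline data collection, families will decide whether to enroll in either the upcoming 10-week session" or to wait 10 weeks. Under Intervention, "Each 90-min lesson is delivered weekly over the dinner hour", and every session includes a group family meal. Under Sample size and data analysis, the groups are compared by "comparing change (T1-T0) in diet quality, anthropometric measures, and blood pressure". The Abstract names change in child diet quality among the main outcomes.

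**The concern.** The telephone window runs forward from the visit and has no stop at lesson 1. Because the visit itself falls in the last 14 days before lesson 1, the two windows overlap the start of the programme. An intervention family's T0 score can then include days after lessons began, even a day on which dinner was the programme's own group meal, which Table 5 describes as covering all five food groups.

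At T0 the waitlist families have no programme, so the error is differential. If the programme improves diet, it raises the T0 score in one group only and shrinks the estimated T1-T0 effect on a main outcome. The intervention group's T1-T0 change is also used in the replication comparison, so the same error enters there. A baseline diet record taken late cannot be collected again.

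**Working it through.** The article gives no figure to reproduce. The check is calendar arithmetic on its stated windows.

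**Inputs.** Lesson 1 is day 0 and lesson 2 is day 7 (weekly lessons, Intervention). The visit day v runs from -14 to -1 (Study design). The last permitted call is on day v + 14 (Diet quality). Convention assumed here: a recall covers the day before the call.

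**Step 1: latest permitted recall.** Last call = v + 14; last recalled day = v + 13.

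| Visit day | Last call | Last recalled day | Lessons on or before that day |
|---|---|---|---|
| -14 | 0 | -1 | 0 |
| -13 | +1 | 0 | 1 |
| -10 | +4 | +3 | 1 |
| -7 | +7 | +6 | 1 |
| -3 | +11 | +10 | 2 |
| -1 | +13 | +12 | 2 |

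Only a visit on day -14 guarantees that every recalled day precedes lesson 1.

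**Step 2: earliest possible completion.** The visit recall covers day v - 1. Because recalled days must be nonconsecutive, the next can be v + 1 at the earliest and the third v + 3. All three precede lesson 1 only if v + 3 ≤ -1, that is v ≤ -4. Visits on days -3, -2 and -1 cannot meet this however promptly staff call. The requirement for two weekdays and one weekend day can only tighten it.

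**Step 3: how many recalls, under assumed timing.** The article gives no distribution of visit or call days, so these are illustrations, for intervention families only.

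- *Continuous time.* Let the visit-to-lesson gap be uniform on 0 to 14 days and each call delay uniform on 0 to L days.
  - Share of telephone recalls after lesson 1 = (L/2)/14.
  - Share of all three T0 recalls = two thirds of that.
  - Share of families with at least one = (2L/3)/14, since the mean of the later of two delays is 2L/3.
  - L = 14: 7/14 = 50%; 2 × 0.50/3 = 33%; 9.33/14 = 67%.
  - L = 7: 3.5/14 = 25%; 2 × 0.25/3 = 17%; 4.67/14 = 33%.
- *Whole days.* Let v be uniform on -14 to -1, with two nonconsecutive call days uniform over days 2 to 14 after the visit. A call c days after the visit covers a day on or after lesson 1 with probability (c - 1)/14.
  - Mean c is 8, so 7/14 = 50% of telephone recalls, or one third of all T0 recalls.
  - The mean of the later call is 10.67: 9.67/14 = 69% of families have at least one exposed recall.
  - The mean of the earlier call is 5.33: 4.33/14 = 31% have both exposed.

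**Step 4: what it could do to the contrast.** Suppose an exposed recall carries a share f of the full programme effect, and treat the index as roughly the average of three recalls. In an affected family the T1-T0 effect shrinks by f/3 (one recall) to 2f/3 (two recalls): 8% to 17% at f = 0.25, and 33% to 67% at f = 1. The document gives no value for f.

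**The case against.** The strongest reply is the order of events below Table 1. Families choose their group after baseline data collection, and all three recalls belong to the baseline time point. On that reading every T0 recall precedes group choice and so precedes lesson 1. This shows that a pre-programme baseline was intended. It does not close the telephone window, which is stated separately and tied to the visit, and by Step 2 the intended order is impossible for a visit in the last three days. A reader might infer that recalls are planned after a family has chosen its group; the stated order counts against that, and the point here is only that the provisions conflict.

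It can also be said that two weeks is an upper limit, and that call scheduling belongs in a field manual. That is fair as to how often overlap would occur, but both windows are stated in the article and together they permit it.

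Early exposure may also be weak. In Table 6 the lesson 1 goal is a mealtime game and lesson 2 concerns budgeting; meal balance, drinks, cooking methods and portions come in lessons 5 to 8. This argues for a small f, apart from lesson days, when the programme serves dinner.

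A stronger reading is that waitlist T1 recalls likewise run into that group's own programme, raising the control endpoint. The document does not establish this. The two-week visit window is stated for baseline only, no T1 visit window is given, and Table 1 is not shown. The text is silent on the gap, which justifies a precaution but not a finding of overlap.

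**Conclusion.** The concern holds for T0. The stated windows allow baseline calls up to day +13, covering days up to +12, and visits on days -3 to -1 cannot give three nonconsecutive recalled days before lesson 1. Study design, the text below Table 1 and Diet quality need to be reconciled. The exposure is confined to the intervention group and, if the programme improves diet, biases the T1-T0 diet-quality contrast toward no effect.

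Under uniform timing, about one third of intervention-group T0 recalls and about two thirds of intervention families are affected; with calls within 7 days, about one sixth and one third. These shares rest on assumed timing and should not be read as applying to the whole trial: over all 60 families they halve, because the 30 waitlist families are unexposed at T0. The size of the effect on the Healthy Eating Index cannot be derived from the document.

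**What to change.** State that all three T0 recalls are completed before group choice and before lesson 1. Open the baseline visit window earlier, for example 3 to 4 weeks before lesson 1, so that two weekdays and one weekend day still fit. A visit on day -15 or earlier lets the full 14-day telephone window close by day -1. In a sensitivity analysis, exclude any T0 recall that covers a day on or after lesson 1.

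For the waitlist group at T1, where no gap is stated, start its programme only after its T1 recalls are complete. Keep the T1 recall window the same in both groups, so that the compared intervals do not differ.

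The cost is mainly scheduling: a slightly longer gap between visit and lesson 1 and, if the waitlist T1 visit falls at week 10, up to 14 days' wait before that group starts. A few time points will have fewer than three recalls, and excluding recalls disturbs the weekday and weekend mix, which is why exclusion belongs in a sensitivity analysis. No extra participants or measurements are needed.
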